#### 2.5.2. Overall Data Management 

Management of trial data will be in accordance with a data-management protocol, developed and approved by the nominated advisory group. Data will be stored in accordance with the requirements of the Hunter New England (HNE), University of Newcastle, and Swinburne University of Technology Human Research Ethics Committees (HRECs). All questionnaires and notes will be deidentified and recordings will be stored in a locked HNE Microsoft Teams folder to maintain confidentiality. 

### 2.6. Statistical Analyses

All statistical analyses will be undertaken using SAS v9.2 statistical software. The main data-collection point will be at 6 months post-baseline, as this will be approximately 2 years from the initial introduction of the COVID-19 guidelines. The 12-month timepoint will be used for assessing whether indoor–outdoor free-play programs continue to be delivered following cessation of active sustainment strategy (the SPSH program). For all outcomes, we will assess for normality and use non-parametric test where non-normality is observed.

#### 2.6.1. Acceptability and Feasibility 

Descriptive statistics (mean and standard deviation (SD) or median and range when non-normal) will be generated for both acceptability and feasibility at 6 months post-baseline. For acceptability, individual scores from each domain will be summed (reverse scored where necessary) and used to provide a score for each service. For example, ≤2 will be a negative response, indicating the SPSH program is considered unacceptable, while ≥4 will be a positive response, indicating the SPSH program is considered acceptable. In cases of missing values, we will impute the average scores. Answers to the open-ended question will be analysed qualitatively, using thematic analysis to identify key themes. For feasibility, the individual scores of each of the three items (“the strategy seems possible”, “seems doable” and “seems easy”) will be summed to provide an overall score for each service, in which ≥4 (higher scores) will indicate greater feasibility, while ≤2 (lower scores) will indicate lower feasibility, consistent the recommendations of Weiner et al. (2017) in the Feasibility of Intervention Measure. For the open-ended question, the responses will be analysed qualitatively, using thematic analysis to identify key themes. 

#### 2.6.2. Sustainment of Indoor–Outdoor Free Play

Separate analyses will be performed at each follow-up time point (6 and 12 months post-baseline) for each primary outcome, total minutes of indoor-only free play and total minutes of indoor-outdoor free play. Linear regression models will be used to compare intervention and control group differences, controlling for the baseline outcome data. Alternatively, equivalent non-parametric tests will be performed if linear regression assumptions are not met.. Analyses will follow the intention-to-treat principle and include all data analysed according to the group to which each service was originally randomly assigned. Imputation techniques will be applied where appropriate.

#### 2.6.3. Adoption of SPSH-Program Recommendations

Adoption will be assessed by counting how many strategies were “complete” out of the minimum of 4 strategies in the Sustainability Action Plan during the 6-month program for each service. The minimum requirement for services is to complete at least one goal from the “Notify families and community members of indoor–outdoor free play” strategy, “Notify staff of indoor–outdoor free play” strategy, “Update policy” strategy and “Conduct indoor–outdoor free play as part of daily routine” strategy. The number of completed strategies will be summed to determine how many strategies were completed by each service. A minimum of 4 strategies set as “complete” will be required for the service to have adopted the SPSH program recommendations. After all intervention services have had their action plan counted, a mean will be calculated, showing the average number of services adopting the SPSH program recommendations. 

#### 2.6.4. Feasibility of Trial Methods

Feasibility of the trial methods will be analysed at baseline and 6 months post-baseline. Consent rate, percentage of missing data from completion of the FPR, comparison of consenter/non-consenter characteristics, attrition rate, withdrawal and reasons and contamination will all be analysed using descriptive statistics. 

#### 2.6.5. Fidelity to Delivery of the SPSH Program

Fidelity will be assessed using an internal spreadsheet tracking recruitment and intervention delivery. Each step records time spent, staff involved and whether it has been completed. Analysis will include summing the number of completed steps according to the protocol for each service to determine the degree of implementation according to the original protocol. 

#### 2.6.6. Barriers and Facilitators to the Sustainment 

Barriers and facilitators of sustainment will be analysed at 6 months post-baseline. The outer contextual factors and processes will be scored individually. The total scores (i.e., the mean and SD) of each of the two domains will be calculated. The total scores will be calculated by summing all scores for all items within the subdomain and dividing by the total number of responses within the domain. The higher domain scores (≥4) will be considered facilitators of sustainment, while the lower domain scores (<4) will be considered barriers to sustainment.

#### 2.6.7. Progression Criteria

An advisory group will assess suitability for progression to a fully powered trial using data collected around feasibility of trial methods and outcomes related to potential sustainment, fidelity, and acceptability. These decisions will be made via majority, by core members of the research team, including a representative from a health service that intends to adopt the sustainment strategy if it is found to be beneficial. Specifically, the team must deem the intervention and sustainment strategy to be sufficiently acceptable and feasible for it to be likely to be adopted by approximately 25% of ECEC services to which it is offered (i.e., a consent rate of >25%) [85]. Alternatively, the team may decide that this could be reasonably expected with adaptations to the intervention or sustainment approach, based on steps previously employed [86]. Further, as recommended, measures of delivery of the SPSH program, together with acceptability and feasibility, as well as barriers and facilitators, will be used to identify opportunities to further strengthen the intervention and refine trial methods prior to a fully powered implementation trial.

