### 2.2. Participants and Recruitment

#### 2.2.1. Sampling Frame

The research team undertook a telephone survey with a randomly selected sample of 231 Long Day Care (LDC) services and preschools in NSW from October 2021 to June 2022, of which 99 services met the eligibility criteria for the current study and form the current sampling frame. These LDC services usually operate from 7 a.m. to 6 p.m. Monday through Friday and cater for children from birth to school age, while preschools cater for children aged 3–5 years and operate from 9 a.m. to 3:30 p.m. [28].

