#### 2.2.3. Recruitment Procedures

All services in the sampling frame will receive an invitation email consisting of a recruitment package including an information statement and a link to an online consent form outlining study requirements and requesting participation. Once the consent form has been completed by the nominated supervisor, the online survey will automatically generate the recruitment survey to assess eligibility. A member of the research team will telephone services that have not responded after two weeks of receiving the email to discuss study details, confirm eligibility and request consent for study participation. Recruitment will continue until 20 ECEC services have consented [30,31]. Additionally, the research team will obtain the contact details of an educator who will assist with baseline data-collection processes. 

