#### 2.4.2. Sample Size

As this is a pilot study, a formal sample-size calculation on efficacy was not performed, in line with best-practice guidance [27]. However, the researchers sought to recruit 20 ECEC services, as this number was considered feasible in the timeframe and sufficient to provide an adequate indication of the feasibility and acceptability of study methods and the sustainment strategy [30,31].

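### Read literally, the consent-rate criterion of more than 25% conflicts with inviting 99 services and stopping at 20 consents, which gives about 20.2%

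*Protocol article*

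**What the plan says.** Four parts of the protocol article bear on this.

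- **Frame (2.2.1).** An earlier telephone survey covered 231 services, "of which 99 services met the eligibility criteria for the current study and form the current sampling frame".
- **Offer and stop (2.2.3).** "All services in the sampling frame will receive an invitation email", with a link to the consent form. Then: "A member of the research team will telephone services that have not responded after two weeks of receiving the email". The stop is: "Recruitment will continue until 20 ECEC services have consented". Eligibility is checked again at this stage: after consent, "the online survey will automatically generate the recruitment survey to assess eligibility", and the callers confirm it too.
- **Target (2.4.2).** No formal efficacy calculation was done; "the researchers sought to recruit 20 ECEC services, as this number was considered feasible in the timeframe".
- **Progression (2.6.7).** The strategy must be judged acceptable and feasible enough to be "likely to be adopted by approximately 25% of ECEC services to which it is offered (i.e., a consent rate of >25", that is, more than 25%. The section adds: "Alternatively, the team may decide that this could be reasonably expected with adaptations to the intervention or sustainment approach".

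Sections 2.5.1 and 2.6.4 list the consent rate as a trial-feasibility outcome. Neither gives a denominator different from the one in 2.6.7.

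**The concern.** The progression section expresses its threshold as a share of the services that are offered the program. The recruitment section offers it to the whole frame at the outset, with no release in batches, and then ends recruitment at a fixed count. Numerator and denominator are therefore both close to fixed by design, and their ratio falls below the threshold.

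Informing a fully powered trial is a stated aim of this pilot, and the consent rate is the one progression item with a number attached. If the recorded rate mainly reflects where recruitment was stopped, a shortfall against 25% says little about whether services want the program. The adaptations clause might then be used to answer a shortfall that the cap produced. Conversely, if a narrower denominator was intended but not written down, pass or fail depends on an unstated choice.

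**Working it through.** The article gives no calculated figure to reproduce here; the check is a direct proportion.

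**Inputs.** Services invited: 99 (2.2.1, 2.2.3). Consents at which recruitment stops: 20 (2.2.3, 2.4.2). Threshold: more than 25% (2.6.7).

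**Rate under the plan.** Consents ÷ services offered = 20/99 = 20.2%.

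**Consents needed with 99 offered.** 0.25 × 99 = 24.75, so 25 are needed: 24/99 = 24.2% fails and 25/99 = 25.3% passes. That is 5 more than the stop.

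**Denominator needed with 20 consents.** 20/0.25 = 80, and the inequality is strict, so it must be 79 or fewer: 20/80 = 25.0% does not pass and 20/79 = 25.3% does. At least 99 − 79 = 20 invited services would have to leave the denominator.

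**Sensitivity to the denominator** (illustrative values; the article does not say how many services would remain):

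| Denominator | 20 ÷ denominator |
|---|---|
| 99 | 20.2% |
| 90 | 22.2% |
| 80 | 25.0% |
| 79 | 25.3% |
| 70 | 28.6% |
| 50 | 40.0% |

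**What the cap hides.** Assume each of the 99 services is independently willing with probability p. The chance that at least 20 are willing, so that the stop is reached, is P(X ≥ 20) with X ~ Binomial(99, p):

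| Assumed p | P(X ≥ 20) |
|---|---|
| 25% | 0.89 |
| 30% | 0.99 |
| 40% | >0.999 |

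If recruitment ends at exactly 20, all of these cases record the same 20.2%. The recorded rate therefore cannot tell a true willingness of 25% from one of 30% or 40%.

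**The case against.** The strongest reply is that the article never defines the consent-rate denominator separately, and that a narrower one is plausible. The frame was screened between October 2021 and June 2022 and baseline ran from September to December 2022. The authors themselves expect the practice to fade, and eligibility is checked again at recruitment, so some of the 99 may no longer have qualified. This stands as a possibility. It does not remove the conflict: 2.6.7 refers to services offered the program, the 99 had already been screened as eligible, and at least 20 would have to drop out of the denominator.

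A second reply is that the criterion is a judgement rather than a mechanical gate. That is also right. The decision is by majority, draws on fidelity, acceptability and sustainment data, and may rest on expected adaptations. But 2.6.7 then equates the judgement with a consent rate above a stated figure, and the pilot records a consent rate.

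A third is that the stop limits recruitment effort and is not a proven ceiling. The consent link goes to all services at once, and nothing says that it closes at the 20th consent, so the count could overshoot. It would have to reach 25.

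A reader might go further and infer that the criterion cannot be met under any circumstances, that the pilot must fail, or that its consent data are worthless. The documents do not support this. Re-checked eligibility and overshoot are both open routes to a higher rate, and the adaptations clause leaves progression open. Failing to reach 20 out of 99 would be informative, as would withdrawals with their reasons and the planned comparison of consenters with non-consenters.

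**Conclusion.** The conflict is real on the literal wording. The only numeric progression criterion asks for more than 25% of services offered the program, while the recruitment plan yields about 20.2%, which is 5 consents short. This assumes that all 99 invited services stay in the denominator and that recruitment ends at or close to 20. The finding that the rate cannot discriminate from about 25% upwards also assumes independent, equal willingness across services.

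It is tempting to attach an exact binomial interval to 20/99 (12.8% to 29.5%) and note that it contains 25%. That should not be read as a test of the threshold, because the count of 20 is fixed by the stopping rule and is not a free binomial outcome.

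This should be fixed, but it is not critical: randomisation, data collection and the outcome analyses are unaffected, and progression remains possible by team judgement.

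**What to change.** In 2.6.7 and 2.6.4:

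1. State that recruitment was capped at 20, so consents out of 99 invited is a lower bound on willingness and cannot be tested against the 25% threshold.
2. Apply the threshold to a stated denominator that respects the cap: services still eligible and approached to a resolution by the time of the 20th consent. Resolution means consent, refusal, or non-response after the full email and telephone follow-up. Non-responders who completed that follow-up stay in the denominator.
3. Report separately the services whose follow-up was incomplete at the stop and those found ineligible.
4. Show 20/99 as the lower bound and the responders-only rate, consents ÷ (consents + refusals), as the upper bound.
5. Record the change as a protocol modification made after recruitment. Section 3 already commits to updating the registration record for modifications.

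The cost is a few sentences and one table from existing recruitment records. The downside is that baseline data are collected and the trial is in its delivery stage, so the definition would be set when consent counts can already be known, and it is more favourable than 20/99. Restricting the threshold to definite responders would be more favourable still, since it drops non-responders. All the rates must therefore be shown together.

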## 3. Trial Status

The trial is currently in the intervention-delivery stage. It is not anticipated that any events will occur that would warrant discontinuing the trial as the SPSH program will be delivered completely online. Any unforeseen adverse events would be reported to the HNE HREC (primary approval committee), and appropriate action would be taken to address the event. The trial’s registration record will be updated with any protocol modifications and any deviations from the original protocol will be reported when publishing trial outcomes.

## 4. Discussion

This protocol outlines the development and evaluation of a theory-informed sustainment strategy to increase the sustainment (ongoing implementation) of an evidence-based PA practice (indoor–outdoor programs in ECEC settings). While the sustainment of PA practices in ECEC is needed for continued health improvements in the population and are likely to provide considerable cost savings, there is an absence of empirical evidence on how this can be achieved. This pilot trial seeks to describe, for the first time, the feasibility, acceptability and impact of a program (SPSH) on the sustainment of EBP, providing an insight into how to support the sustainment of health-promotion programs delivered in the ECEC context.

## 5. Conclusions

This protocol outlines the methods and development of a strategy to improve the sustainment of outdoor-free-play opportunities through ECEC services. The application of the strategy will provide important proof-of-concept data to support the conduct of a fully powered trial, the first of its kind, as well as informing the development of future sustainment strategies in ECEC settings more broadly.

## Figures and Tables

**Table 1 ijerph-20-05043-t001:** Mapping of sustainment strategies against the Integrated Sustainability Framework and the Action, Actor, Context, Target, Time (AACTT) Framework [25,37].

Sustainment Strategy	Strategy Description (*ERIC Strategy and Definitions*) [35]	Actor(s)/Personnel	Context	Target	Time	Integrated Sustainability Framework Domain + Factor [25]	Barriers Addressed [34]	Justification
Identify opinion leaders at the service	*ERIC Strategy: Engage with local opinion leaders.* *Periodically engage with providers identified by colleagues as opinion leaders or “educationally influential” about the importance of continuing to deliver the practice innovation in the hopes that they will influence colleagues to sustain its use.* The identification of and engagement with a staff member who could be considered as a key driver or influencer in the original implementation of the EBP.	Health-promotion officer/nominated supervisor	Phone call	Opinion leader	Prior to the introductory-meeting video call	Inner Contextual Factors *Organisational leadership and support*	Lack of administrative buy-in and support/ leadership/management ^a^ [38,39,40,41,42,43,44]	The identification of an opinion leader is intended to target these barriers around leadership/support from management by identifying a staff member at the service who can lead the sustainment strategy to encourage and motivate other staff to continue to deliver indoor-outdoor free play programs.
						Inner Contextual Factors *Programme champions*	Lack of programme leaders/facilitators/champions ^a^ [38,43]	
Affirm intent of continuity	*ERIC Strategy: Affirm formal commitments.* *Revisit the written commitments obtained from key partners that state what they will do to implement and sustain the innovation. Assess whether these commitments are being upheld and whether new commitments are required to help sustain the innovation.* The level of commitment to ongoing implementation will also be ascertained by establishing service motivations for initial and continued implementation, as well as understanding any barriers and facilitators to the long-term implementation of the EBP and the sustainment strategies. This will be developed using the following strategies: Sustainability Action Plan; Motivational statement.	Health-promotion officer	Video calls/phone calls	Opinion leader	Introductory-meeting video call Three-month support meeting Additional contacts upon request	Characteristics of interventionists and population *Implementer characteristics*	Lack of motivation/interest ^a^ [41,44,45,46,47]	Affirming the services intent to continue helps to tackle the lack-of-motivation barrier by regularly reminding the service of the importance of indoor–outdoor free-play programs and their benefits to children.
						Characteristics of the intervention *Perceived benefits*	Limited cost-effectiveness/feasibility of program ^a^ [41] Time required to implement and record uptake of the program ^a^ [45] Competing resources, responsibilities and curriculum demands ^a^ [39,41,43,44,45,48]	This strategy also targets the barriers to feasibility of the EBP, the time required to implement the EBP and competing responsibilities, as it focuses on re-iterating the services’ intent to continue their practice of delivering indoor–outdoor free play programs. This is important as it highlights that the service is already implementing the EBP; thus, this strategy of the SPSH program aims to aid the services to continue their current practices rather than change routines or add to staff workload.
Provide local technical assistance to support integrating strategies	*ERIC Strategy: Provide local technical assistance.* *Develop and use a system to deliver technical assistance focused on implementation and sustainment issues using local personnel.* Opinion leader will receive 2 video-call-support meetings and a minimum of 2 emails throughout the intervention period. The initial video meeting will highlight the purpose and sustainment strategies. Each contact will review progress and provide feedback on integration of sustainment strategies. Additional support will be provided as required.	Health promotion officer	Introductory/3-month support meeting: Video call Other intervention contacts (as required): phone/email	NS/Opinion leader	One video call at beginning of intervention and at the 3-month timepoint One email at the 2- and 4/5-month timepoints	Processes ^b^ *Training/supervision/support*	Lack of training/professional development opportunities to upskill ^a^ [41,42,43,46,47,49,50]	The provision of technical support aims to target this barrier through providing services with the skills/tools thar are needed to continue to implement the EBP themselves without external support.
						Processes ^b^ *Programme evaluation/data*	Lack of clear data on effectiveness of program ^a^ [45]	In the case of clarity around the effectiveness of the EBP, technical support is provided to develop a motivational statement supporting the delivery of the EBP, to ensure services understand the importance of this practice. In addition, this strategy aims to address any challenges experienced when delivering the EBP.
Develop a formal sustainment blueprint	*ERIC Strategy: Develop a formal implementation blueprint.* *Develop a formal blueprint which includes all goals and strategies to guide the implementation effort over time.* This is the introduction of an action plan (“Sustainability Action Plan”) for the service to implement best-practice sustainment strategies. This will track the implementation of the sustainment strategies and their progress.	Health promotion officer and Opinion leader	Introductory/3-month support meeting: Video call	Opinion leader	Provided: prior to introductory support call Discussed: during the introductory and 3-month support meeting Action: self-directed throughout the 6-month intervention period	Inner Contextual Factors *Organisational leadership/support*	Lack of centralised coordination ^a^ [39]	This aims to address these barriers by developing a Sustainability Action Plan, with defined strategies, to support the ongoing implementation of the EBP in the long term. The action plan is intended to be a self-directed tool that services use to track their progress in implementing the sustainment strategies, for which the opinion leader is responsible. This strategy allows more centralised leadership, led by the service, rather than externally.
						Processes ^b^ *Communications and strategic planning*	Absence of plan with defined measures ^a^ [45]	
Distribute educational materials	*ERIC Strategy: Distribute educational materials.* *Distribute educational materials (including guidelines, manuals, and toolkits) in person, by mail, and/or electronically.* A resource pack will be provided to services, which will include the following resources: Which external organisations support outdoor free play? How outdoor free play aligns with the National Quality Framework; COVID-19 outdoor-play guidance; Australian Physical Activity guidelines; Indoor–Outdoor Free Play in any Weather fact sheet; Benefits of Outdoor Free Play fact sheet; Shade and Heat fact sheet.	Health promotion officer	Email	Opinion leader	Provided: prior to introductory support meeting Discussed: during introductory support meeting	Outer Contextual Factors ^b^ *Funding environment and availability*	Lack of future external funding/financial support ^a^ [39,40,44,45,51,52]	The resource pack includes a fact sheet on a number of organisations that help ECEC services to deliver and encourage outdoor free play.
						Outer Contextual Factors ^b^ *Sociopolitical context*	Lack of state requirements ^a^ [47,53,54]	The resource pack includes the requirements of outdoor free play in the National Quality Framework and the Early Years Learning Framework, which are part of the accreditation standards for ECEC services in Australia.
						Outer Contextual Factors ^b^ *Values, needs, priorities*	Lack of evidence-based treatments ^a^ [39] Government perceptions ^a^ [45]	The “benefits of outdoor free play” fact sheet highlights the importance of the EBP through an evidence-based lens. Government perceptions are addressed through the fact sheets on the Australian government supporting outdoor free play through the Australian physical activity guidelines and the NSW COVID-19 outdoor-free-play guidance for ECEC services.
						Processes ^b^ *Training/supervision/support*	Lack of training/professional development opportunities to upskill ^a^ [41,42,43,46,47,49,50]	The Indoor–Outdoor Free Play in any Weather fact sheet and the Shade and Heat fact sheet highlight the different ways in which children can enjoy the outdoors in different seasons while staying safe. This strategy addresses this barrier by exploring the different ways in which indoor–outdoor free-play programs can be implemented at an ECEC service.
						Processes ^b^ *Programme evaluation/data*	Lack of clear data on effectiveness of program ^a^ [45]	These barriers are addressed through the Benefits of Outdoor Free Play fact sheet, highlighting the importance of outdoor free play for children due to the many benefits children receive. This EBP is strongly considered in the literature to be an effective way to increase PA, which in turn has many health benefits for children.
Engaging with families	*ERIC Strategy: Involve patients/consumers and family members.* *Engage or include patients/consumers and families in the implementation and sustainment efforts.* The following resources will be provided to services: Orientation-package templates for new families and staff; Template for advocating the EBP on the services’ website; Newsletter snippets for families.	Health-promotion officer/ Opinion leader	Email/Video call	Families /staff at the service Community members	Provided: prior to introductory support meeting Discussed: during introductory support meeting Action: self-directed throughout the 6-month intervention period	Processes ^b^ *Partnership/* *engagement*	Lack of collaboration with community groups ^a^ [43]	The use of the newsletter snippets and orientation packages for families allow the services to communicate with families and the community regarding the delivery of indoor–outdoor free-play programs in their respective service setting. This communication opens up opportunities for families to weigh in and provide feedback, as well as to promote the benefits of this practice to community members. In this way, barriers such as lack of collaboration with communities, communicating information and lack of parental buy-in are addressed.
						Processes ^b^ *Communications and strategic planning*	Communicating information to stakeholders^a^ [51]	
						Characteristics of the interventionists and population *Population characteristics*	Lack of parental buy-in/support (e.g., uninterested parents) ^a^ [41,43,44,45]	
						Inner Contextual Factors *Organisational stability*	Staff turnover ^a,c^ [22,38,41,44,55]	By advocating for the delivery of indoor–outdoor free-play programs on the services’ websites and the provision of orientation packages for new staff, the barrier of staff turnover is addressed, as new staff members are aware of the current practices and, therefore, should continue to uphold these as new members of their respective teams.
Review and embedding change into policy	*ERIC Strategy: Mandate change.* *Have leadership declare the priority of the innovation and their determination to have it implemented and sustained.* The following resources will be provided to services: Policy template for indoor-outdoor free play programs; Policy checklist.	Health-promotion officer/ Opinion leader	Email	Staff at the service/Service routine/Service policy	Provided: prior to introductory support meeting Discussed: during the 2-month and 4-month policy review email Action: self-directed throughout the 6-month intervention period	Inner Contextual Factors *Organisational leadership/support*	Lack of centralised coordination ^a^ [39]	To address these barriers, the provision of a policy template that outlines the benefits of indoor–outdoor free-play programs and their consistent provision enables services to implement changes to their service policies. By allowing services to formally integrate the EBP into their service policies, staff members will be able to develop a set of procedures to ensure the provision of indoor–outdoor free-play programs as part of their daily routine.
						Processes ^b^ *Training/supervision/support*	Lack of training/professional development opportunities to upskill ^a^ [41,42,43,46,47,49,50]	
	Reviewing and embedding the practice of indoor–outdoor free-play programs in the service routine as a strategy on the “Sustainability Action Plan”.	Health-promotion officer/Opinion leader	Email	Staff at the service/Service routine/Service policy	Provided: prior to introductory support meeting Discussed: during the 2-month and 4-month policy review email Action: self-directed throughout the 6-month intervention period	Processes ^b^*Communications and strategic planning*	Absence of plan with defined measures ^a^ [45]	The “review policy” strategy in the Sustainability Action Plan will allow services the opportunity to review their current service policies and embed the regular practice of providing indoor–outdoor free-play programs as part of their daily routine. This strategy will provide services with a plan to ensure the provision of indoor–outdoor free-play programs in the long term.
Develop and implement tools for quality monitoring	*ERIC Strategy: Develop and implement tools for quality monitoring. Develop, test, and introduce into quality-monitoring systems the right input—the appropriate language, protocols, algorithms, standards, and measures (of processes, patient/consumer outcomes, and implementation outcomes) that are often specific to the innovation being implemented and sustained.* At the initial contact, an “ongoing monitoring plan” item will be added to the Sustainability Action Plan.	Health-promotion officer/Opinion leader	Email/Video call	Staff at the service	Provided: prior to introductory support meeting Discussed: during introductory support meeting and 3-month support meeting Action: self-directed throughout the 6-month intervention period	Processes ^b^ *Programme evaluation/data*	Accuracy in assessing impact of program ^a^ [45,51] Lack of clear data on effectiveness of program ^a^ [45]	The use of an ongoing monitoring tool, such as the FPR, will enable services to monitor their ongoing delivery of the EBP. This tool will highlight the gaps in indoor–outdoor free-play provision and address the lack of professional-development opportunities to upskill. In this way, staff will have the opportunity to self-monitor and adjust their practices. By using an ongoing monitoring tool, services will be able to accurately assess the impact of the program through child benefits, family feedback or other measures, thus enabling the identification of the effectiveness of indoor–outdoor free-play programs.
						**Processes** ^b^ *Communications and strategic planning*	Absence of plan with defined measures ^a^ [45]	

^a^ Barriers identified from interventions in schools [34]; ^b^ barriers identified from the NSW CATI (see intervention components); ^c^ barriers identified from interventions in ECEC settings [34].

**Table 2 ijerph-20-05043-t002:** Intervention schedule.

Month	Type of Contact	When	Method	Resources
0	Admin	Recruitment	Email	Recruitment pack
0	Admin	Recruitment	Call	Nominated-supervisor recruitment survey
0	Admin	Recruitment	Email	Free-play record
0	Admin	Recruitment	Email	Allocation email Opinion Leader position description
1	Admin	Baseline	Call	Administrative contact to book 1st intervention contact and identify Opinion Leader
1	First intervention contact	One-month timepoint Introductory meeting	Videoconference call	Introductory-meeting script Resource pack Sustainability action plan Guidance for addressing barriers
1	Admin	One-month timepoint after introductory support meeting	Email	Introductory-support-call summary email
1	Second intervention contact	Two-month timepoint Policy Review #1	Email	Service policy Policy template Policy checklist Policy feedback Policy review email
3	Admin	3-month timepoint Reminder email	Email	Three-month timepoint reminder email
3	Third intervention contact	3-month timepoint Support meeting	Videoconference call	Guidance for addressing barriers Sustainability action plan
3	Admin	Three-month timepoint After Support meeting	Email	Three-month support call summary email
4–5	Fourth intervention contact	Four/five-month timepoint Policy Review #2	Email	Service policy Policy template Policy checklist Policy feedback Policy-review email
	Additional contacts	As needed throughout the intervention period	Email/Call/Videoconference call	As needed
6	Follow-up	Six-month post-baseline timepoint End of intervention	Email/Call	Free-play record Sustainability action plan
		As needed throughout the intervention period		As needed
12	Follow up	Twelve-month timepoint	Email/Call	Free-play record Sustainability action plan

**Table 3 ijerph-20-05043-t003:** Feasibility and Acceptability measurement.

Intervention acceptability and feasibility (intervention services only)					
Over the last 6 months, your service was provided with support to continue to provide opportunities for indoor–outdoor free play in an ongoing way, as part of our program known as Sustaining Play, Sustaining Health. We are interested in your experience, and the acceptability and feasibility of the support provided to your service as part of this program. There are no right or wrong answers. We are interested in your beliefs and perceptions. By answering these questions, you will help us to identify what support may assist services in the ongoing delivery of health programs. We will ask you to answer each question using a scale from 1 to 5.					
TFA construct	Generic TFA questionnaire items				
Affective attitude How you felt about the program	A1. Did you like or dislike the Sustaining Play, Sustaining Health program?				
	Strongly dislike	Dislike	No opinion	Like	Strongly like
	1	2	3	4	5
Burden The amount of effort required to participate in the program	A2. How much effort did it take to engage with the Sustaining Play, Sustaining Health program?				
	No effort at all	A little effort	No opinion	A lot of effort	Huge effort
	1	2	3	4	5
Perceived effectiveness The extent to which the prograe is perceived to have achieved its objective	A3. The Sustaining Play, Sustaining Health program has helped to continue the sustainment of indoor–outdoor free-play routines.				
	Strongly disagree	Disagree	No opinion	Agree	Strongly agree
	1	2	3	4	5
Intervention coherence The extent to which the participant understands how the program works	A4. It is clear to me how the Sustaining Play, Sustaining Health program has helped to continue the sustainment of indoor–outdoor free-play routines at my service.				
	Strongly disagree	Disagree	No opinion	Agree	Strongly agree
	1	2	3	4	5
	Please tell us more about your views				
Self-efficacy A participant’s confidence that they can perform task(s) required to participate in the program	A5. How confident did you feel about participating in the Sustaining Play, Sustaining Health program?				
	(i.e., How confident did you feel about using the sustainability strategy to continue to deliver indoor-outdoor free play routines at your service?)				
	Very unconfident	Unconfident	No opinion	Confident	Very confident
	1	2	3	4	5
Opportunity costs The benefits, profits or values that would have to be given up to engage with the program	A6. Participating in the Sustaining Play, Sustaining Health program interfered with my other priorities				
	(i.e., Did implementing the sustainability strategy interfere with your other priorities?)				
	Strongly disagree	Disagree	No opinion	Agree	Strongly agree
	1	2	3	4	5
General acceptability	A7. How acceptable was the Sustaining Play, Sustaining Health program to you?				
	Completely unacceptable	Unacceptable	No opinion	Acceptable	Completely acceptable
	1	2	3	4	5
A8. Is there anything further you would like to mention regarding how acceptable the Sustaining Play, Sustaining Health program was at your service?					
Feasibility	F1. Continuing to implement the sustainability strategy used in the Sustaining Play, Sustaining Health program seems possible.				
	Strongly disagree	Disagree	No opinion	Agree	Strongly agree
	1	2	3	4	5
	F2. Continuing to implement the sustainability strategy used in the Sustaining Play, Sustaining Health program seems doable.				
	Strongly disagree	Disagree	No opinion	Agree	Strongly agree
	1	2	3	4	5
	F3. Continuing to implement the sustainability strategy used in the Sustaining Play, Sustaining Health program seems easy.				
	Strongly disagree	Disagree	No opinion	Agree	Strongly agree
	1	2	3	4	5
F4. Is there anything further you would like to mention regarding how feasible the Sustaining Play, Sustaining Health program was at your service?					

